# A prospective, single-centre, randomized, double-blind controlled study protocol to study whether long-term oral metronidazole can effectively reduce the incidence of postoperative liver metastasis in patients with colorectal cancer

**DOI:** 10.1186/s13063-023-07628-y

**Published:** 2023-12-04

**Keywords:** Colorectal cancer, Liver metastasis, Metronidazole, Protocol, Therapy

## Abstract

**Introduction:**

Fifteen to 25% of patients with colorectal cancer have combined liver metastases at the time of diagnosis, whereas an additional 15 to 25% will develop liver metastases after curative resection of primary colorectal cancer, with the vast majority (80–90%) of liver metastases unresponsive to curative resection at first. Colorectal cancer liver metastasis is also the leading cause of death in patients with colorectal cancer. In recent years, several studies have demonstrated that intestinal flora, especially *Fusobacterium nucleatum*, plays a crucial role in the development of colorectal cancer liver metastasis, so we hypothesized that long-term metronidazole use could effectively reduce the incidence of postoperative liver metastasis in colorectal cancer patients.

**Methods/design:**

This study is a prospective, single-centre, randomized, double-blind controlled study in which 300 patients will be randomly assigned to the test group or the control group in a 1:1 allocation ratio. The aim of this trial is to demonstrate that long-term oral antibiotics can effectively reduce the incidence of postoperative liver metastasis in patients with colorectal cancer.

**Ethics and dissemination:**

Ethics approval was obtained from the Ethics Committee at the Chinese Ethics Committee of Registering Clinical Trials (ChiECRCT20210229). The results of this study will be disseminated at several research conferences and as published articles in peer-reviewed journals.

**Trial registration:**

Chinese Clinical Trial Registry ChiCTR2100046201. Registered on July 05, 2021.

**Supplementary Information:**

The online version contains supplementary material available at 10.1186/s13063-023-07628-y.

## Introduction

The liver is the most prominent target organ for haematogenous metastasis of colorectal cancer. Fifteen to 25% of patients with colorectal cancer have combined liver metastases at the time of diagnosis, and an additional 15 to 25% will develop liver metastases after curative resection of primary colorectal cancer, with the vast majority (80–90%) of liver metastases unresponsive to curative resection at first. Colorectal cancer liver metastasis is also the leading cause of death in patients with colorectal cancer.

In 2006, a review [1] that summarized relevant articles from 1991 to 2004 concluded that the search for specific bacteria among the normal flora of bacteria is a reasonable way to evaluate the role of bacteria in chronic inflammatory diseases and related cancers. The ability of complex bacterial flora to cause inflammation or cancer may depend on the aggregate activity of multiple components of the flora, rather than a single species, and this ability may be enhanced or diminished with significant changes in species diversity and abundance within the flora. In 2012, an article suggested that chronic inflammation in the gut can affect colorectal carcinogenesis by altering the gut microbial composition to contribute to CRC development [2]. Their study showed that inflammation alters the host physiological status to promote the development of cancer, as seen in colitis-associated colorectal cancer, and identified gut microbiota as a target of inflammation that influences CRC progression. Subsequent studies from multiple cohorts around the world identified a large enrichment of *Fusobacterium nucleatum* in faecal samples of colorectal cancer patients by full-throughput sequencing technology [1, 3–6], and in 2017, Matthew Meyerson et al. [7] validated this by establishing a xenogeneic colorectal cancer mouse model, which confirmed that increased abundance of *Fusobacterium nucleatum* in colorectal cancer patients promoted colorectal carcinogenesis as well as the metastatic process. In 2017 [8], a study found that *Fusobacterium nucleatum* was abundant in colorectal cancer tissues of patients with recurrence after chemotherapy and was correlated with the clinicopathological characteristics of patients. Through bioinformatics and functional studies, *Fusobacterium nucleatum* was found to enhance the chemoresistance of colorectal cancer cells by targeted activation of TLR4 and MyD88 (myeloid differentiation factor) as well as specific microRNAs to activate autophagy pathways, which ultimately alters the chemotherapeutic prognosis in patients. *Fusobacterium nucleatum* has a powerful driving effect on colorectal carcinogenesis, and in addition, as an important intratumoral bacterium, *Fusobacterium nucleatum* is involved in tumour progression and mediates tumour resistance to chemotherapeutic drugs. The mechanism by which *Fusobacterium nucleatum* promotes colorectal carcinogenesis was further investigated by Ge Zhang in 2017 [9], which proposed that exosomes derived from *Fusobacterium nucleatum*-infected cells played a role in promoting cancer initiation and progression. All the above studies have shown that the composition and abundance of gut microbiota play a crucial role in the development of CRC, and the currently known microbiota with distinct effects on CRC tumorigenesis are mainly *Escherichia coli* and *Fusobacterium nucleatum*.

Can we reduce the effect of *Fusobacterium nucleatum* on colorectal carcinogenesis by subjecting patients to long-term metronidazole treatment in the clinical setting? Therefore, we hypothesize that long-term oral metronidazole treatment can reduce the incidence of postoperative recurrence and metastasis. This hypothesis is based on the research progress of the correlation between intestinal flora and the occurrence and development of colon cancer.

A 2017 study by Jing Yuan Fang et al. [8] reported that colorectal tumours with a high Fusobacterium load were more prone to recurrence, and a 2017 study [7] demonstrated that treatment of Fusobacterium-positive human colorectal cancer xenograft mouse models with metronidazole could significantly reduce the Fusobacterium load and inhibit cancer cell proliferation and tumour growth. This conclusion somewhat supports our idea that Fusobacterium-positive tumours may benefit from anti-fusobacterial therapy, such as prolonged metronidazole administration.

Based on an examination of the literature, a review published in 2006, by Carlo et al., proposed that long-term metronidazole supplementation is the therapeutic basis for methylmalonic acid (MMA) and propionic acidemia (PA). In 2014, the Society for the Study of Inborn Errors of Metabolism (SSIEM) designated a panel on recommendations for the diagnosis and treatment of methylmalonic acid (MMA), and propionic acidemia (PA), which suggested metronidazole as one of the recommended therapeutic agents; it should be taken lifelong, on a regimen of 10–20 mg/kg/day for 1–2 or 2–3 weeks per month to avoid the emergence of resistant organisms [10].

The long-term effects of metronidazole use cause serious side effects and have been reported as individual cases in recent years. The probability of developing peripheral neuropathy in patients who continue to take metronidazole for > 4 weeks (taking a total dose of > 42 g) for a long period of time is approximately 17.9% [11, 12]. According to calculations, the blood concentration is approximately 34–45 μg/ml when patients develop peripheral neuropathy, and nearly all patients experience symptom resolution after discontinuing the medication. Therefore, for this study, we set the duration of metronidazole administration to 5 years in our patients, and because anaerobes are extremely sensitive to metronidazole, the dosage was extremely low, and in addition to long-term regulatory follow-up, patients in this protocol only needed to maintain daily blood concentrations greater than 0.01 μG/ml, which can maximize patient safety. At the same time, all the studies with patients who showed drug-related adverse reactions were discontinued, which was included in the ITT set and not included in the PP set.

The aim of this prospective, single-centre, large sample, randomized controlled trial is to demonstrate that long-term oral antibiotics can effectively reduce the incidence of post-operative liver metastasis in patients with colorectal cancer. Secondary objectives included safety and acceptability of the drugs used, treatment-related morbidity and mortality, and relevant follow-up.

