
### Interventions

Metronidazole/placebo: Treatment regimens were developed on their own according to each centre’s metronidazole specifications, which required maintenance of metronidazole plasma concentrations for subjects in the experimental group to be > 0.01 μG/ml, and the duration of administration was tentatively set at 5 years (i.e., the time of the outcome of this experiment).

The chemotherapy regimen is eFOLFOX_6_:

Oxaliplatin 85 mg/m^2^ IV infusion for 2 h, D1; leucovorin 400 mg/m^2^ IV for 2 h, D1; fluorouracil 400 mg/m^2^ IV bolus on D1 followed by 1200 mg/m^2^/DX2 continuous IV infusion (total 2400 mg/m^2^ over 46–48 h infusion). This process was repeated every 2 weeks for a total of 24 weeks (Table 1).

**Table 1 Tab1:** Chemotherapy regimen

Drug name	Dose	Timing of the drugs (a total of 28 days/cycle)							
		Pre-operation	Post-operation						
		D3–D1	D1	D2	D3–D14	D15	D16	D17–D21	D22–D28
Metronidazole/placebo	1 g	√	√	√	√	√	√	√	-
Oxaliplatin	85 mg/m^2^		√	-	-	√	-	-	-
Leucovorin	400 mg/m^2^		√	-	-	√	-	-	-
Fluorouracil	400 mg/m^2^		√	-	-	√	-	-	-
Fluorouracil	2400 mg/m^2^(total)		√		-	√		-	-

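### The very-low-dose safety argument for 5 years of metronidazole does not fit the 1 g in Table 1, and the text does not fix one binding regimen

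*Protocol article*

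**What the plan says.** The Introduction reports that in patients who take metronidazole for more than 4 weeks, with a total above 42 g, the probability of peripheral neuropathy "for a long period of time is approximately 17.9"%. When neuropathy appears, "the blood concentration is approximately 34–45" μg/ml, and "nearly all patients experience symptom resolution after discontinuing the medication". It then sets dosing at 5 years, on two grounds: "because anaerobes are extremely sensitive to metronidazole, the dosage was extremely low", and "patients in this protocol only needed to maintain daily blood concentrations greater than 0.01" μg/ml. The second is presented as giving patients the greatest safety.

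A little earlier, the Introduction cites lifelong use in inherited metabolic disease as a precedent, "on a regimen of 10–20 mg/kg/day for 1–2 or 2–3 weeks per month".

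The Interventions section gives the regimen twice:

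- In the text: "Treatment regimens were developed on their own according to each" centre's own metronidazole specifications, "which required maintenance of metronidazole plasma concentrations for subjects in the experimental group" to stay above 0.01 μg/ml, for a tentative 5 years.
- In Table 1, which is titled as the chemotherapy regimen and uses 28-day cycles: metronidazole or placebo 1 g, ticked on D3 to D1 before surgery and D1 to D21 after it, with no dose on D22 to D28.

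Chemotherapy lasts 24 weeks. Table 2 ticks administration up to months 48 to 60.

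**The concern.** The safety case for long dosing rests on the dose being very low, yet the only dose in the article is 1 g. The only concentration rule is a lower bound. A lower bound guards against giving too little and says nothing about giving too much, so it cannot carry a claim about toxicity.

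The centre-set wording and the fixed 1 g also differ as definitions of the treatment. If both stand, the dose under test is not uniquely defined. At stake are what patients receive and the exposure against which the data monitoring committee judges neuropathy.

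**Working it through.** **Inputs.** From the Introduction: 42 g and 4 weeks, 34–45 μg/ml, the 0.01 μg/ml floor, and 10–20 mg/kg/day for up to 2–3 weeks per month. From Interventions and Table 1: 1 g, three pre-operative days, D1 to D21 of 28 days, and 24 weeks of chemotherapy. The 42 g figure is cited from the literature, so the article has no inputs from which to reproduce it.

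**Assumption.** 1 g per ticked day. Table 1 gives no time unit.

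**1. Dose by body weight.** 1,000 mg ÷ 20 mg/kg = 50 kg and 1,000 mg ÷ 10 mg/kg = 100 kg. Between 50 and 100 kg, 1 g a day lies inside the long-term regimen that the Introduction cites, and three weeks in four lies at the long end of its schedule.

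**2. When 42 g is passed.**

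| Post-operative day | With 3 g before surgery | Without |
|---|---|---|
| 21 | 24 g | 21 g |
| 46 | 24 + 18 = 42 g | 21 + 18 = 39 g |
| 47 | 43 g | 40 g |
| 49 | 45 g | 42 g |
| 57 (third cycle starts) | 46 g | 43 g |

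The total first exceeds 42 g on day 47, or on day 57 without the pre-operative doses. Both days fall within the 24 weeks (168 days, 6 cycles). The total over that period is 6 × 21 = 126 g, or 129 g with the pre-operative doses, which is 3.0 to 3.07 times 42 g.

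**3. Does the rest of the condition match?** The longest dosing run is 21 days, or 3 + 21 = 24 with the pre-operative days, against 28 days for 4 weeks. The mean dose is 21 g ÷ 28 days = 0.75 g/day. Taking 42 g in exactly 4 weeks implies 42 ÷ 28 = 1.5 g/day. Table 1 therefore runs at half that rate, with breaks.

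**4. The floor against the neuropathy level.** 34 ÷ 0.01 = 3,400 and 45 ÷ 0.01 = 4,500.

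**5. Sensitivity to the assumption.** If 1 g applied to each ticked column, each cycle would give 6 g. The 24 weeks would give 6 × 6 = 36 g, or 37 g with the pre-operative column, which is below 42 g. If the schedule continued, 42 g would be passed in cycle 7 (cycle 8 without the pre-operative column). At 1 g per cycle it would be passed in cycle 43, after about 3.2 years. The day 47 and day 57 figures thus depend on the per-day reading.

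**The case against.** The strongest objection is that 17.9% belongs to a joint condition, more than 4 weeks and more than 42 g, and that a schedule of 21 days on and 7 off does not clearly meet its first half. This stands. A reader might infer that 17.9% of the metronidazole arm would develop neuropathy. The documents do not support that, and no case count should be drawn from the rate.

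A reader might also multiply Table 1 out to 5 years. Table 1 is titled for chemotherapy, which lasts 24 weeks, and no dose is stated for later years, so a 5-year total is not established. Nor can it be said that 1 g brings levels to 34–45 μg/ml, because the article gives no concentration at that dose.

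The reference to centre specifications may mean only tablet strength. In that case the text and Table 1 agree. The article also calls the trial single-centre, which weakens the worry about differing regimens, although its Randomization and Auditing sections refer to several centres. This objection stands as a possibility that the wording does not settle.

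It is tempting to say that a daily level above the floor conflicts with the drug-free D22 to D28. That needs elimination data that the article does not give, so it is a question to clarify and not a proven conflict.

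The safeguards are real. Patients with drug-related reactions are discontinued (Introduction, and the termination criteria under Eligibility criteria). Drug-related events are a main indicator, and the dose is openly called hypothetical (Primary outcome). Safety is recorded throughout (Table 2, Safety), and data are reviewed every 3 months (Auditing). The cited precedent also gives some support for intermittent long-term use. But these measures respond to harm once it appears, and the precedent is for an ordinary dose. Neither makes 1 g very low.

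**Conclusion.** The concern holds in a limited form. The low-dose claim is not supported by the 1 g in Table 1, and the 0.01 μg/ml floor cannot support the claim of greatest safety. The mismatch with the cited 10–20 mg/kg/day and the crossing of 42 g on day 47 or 57 both assume 1 g per ticked day. The point about the floor needs no such assumption. The dose under test is not uniquely defined unless the centre specifications mean tablet strength alone.

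Nothing here shows that the dose is unsafe or that a particular neuropathy rate will follow. The text should be corrected, but the point ranks below a must-fix. Confidence is moderate, because Table 1 leaves the unit open and the full protocol may say more.

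**What to change.** - Make one regimen binding in both the Interventions text and Table 1, for example 1 g per day on D1 to D21 of 28 days, with centres free only in tablet strength.
- State the dose that applies after the 24 chemotherapy weeks.
- Replace the claims of very low dosage and greatest safety with the planned cumulative exposure, set against 42 g and 34–45 μg/ml. For the example regimen this is 126 to 129 g over the first 24 weeks. Add that the 17.9% rate may not carry over to intermittent dosing and that symptoms nearly always resolve on stopping.
- Say whether the daily concentration requirement applies on D22 to D28.
- Keep the existing discontinuation rules, safety recording and 3-monthly review. The choice of dose stays with the sponsor.

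The cost is a text amendment and one sponsor decision, with no extra patients or visits. The stated safety rationale becomes less favourable, and centres lose some freedom to adapt the regimen to their own product.

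### The Introduction defends five years of metronidazole by a very low dose and a plasma minimum, but the only printed dose is a therapeutic one and a minimum cannot support a safety claim

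*Protocol article*

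**What the plan says.** The Introduction of the protocol article first reports the neurological risk of prolonged use. It gives the probability of peripheral neuropathy with use "for > 4 weeks (taking a total dose of > 42 g) for a long period of time is approximately 17.9"%, puts the blood concentration at onset at roughly 34–45 μg/ml, and adds that "nearly all patients experience symptom resolution after discontinuing the medication".

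It then justifies five years of treatment: "because anaerobes are extremely sensitive to metronidazole, the dosage was extremely low", and patients "only needed to maintain daily blood concentrations greater than 0.01" μg/ml, "which can maximize patient safety".

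A little earlier, the Introduction cites a precedent for long use in inborn errors of metabolism: "it should be taken lifelong, on a regimen of 10–20 mg/kg/day for 1–2 or 2–3 weeks per month".

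The Interventions section leaves regimens to each centre's "metronidazole specifications, which required maintenance of metronidazole plasma concentrations for subjects in the experimental group to be" above 0.01 μg/ml, and says that "the duration of administration was tentatively set at 5 years". Table 1 in that section is titled as the chemotherapy regimen. It prints the only study dose: metronidazole or placebo, 1 g, ticked for the three preoperative days and for postoperative D1 to D21, and not for D22–D28 of the 28-day cycle. Chemotherapy runs for 24 weeks. The Primary outcome section describes the dose as hypothetical and makes drug-related adverse events a main indicator.

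**The concern.** Two printed statements about exposure do not agree. The rationale speaks of a very low dose; the schedule prints a gram on three weeks of every four. The plasma criterion offered in support is a lower bound. A lower bound shows that enough drug is present and says nothing about too much: a patient at 40 μg/ml, inside the range that the article links to neuropathy, would satisfy it.

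The 150 patients of the experimental group are to take the drug for five years. Investigators and ethics reviewers who rely on the Introduction would take the planned exposure to be much lower than Table 1 implies. The centre-set regimens are also bounded only from below.

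**Working it through.** The article states no cumulative dose, so there is no figure of its own to reproduce. The check builds the exposure from Table 1.

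**Inputs.** From Table 1: 1 g per dosing day, 3 preoperative days, 21 dosing days per 28-day cycle. From Interventions: 24 weeks of chemotherapy. From the Introduction: a 42 g marker, 34–45 μg/ml at neuropathy onset, a 0.01 μg/ml minimum, and a reference regimen of 10–20 mg/kg/day for up to 2–3 weeks per month. Assumed: 1 g is a daily total; body weight is 50–100 kg; D1 is the first postoperative day; 1 g applies at every centre.

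**Dose per kilogram.** 1,000 mg / weight:
- 50 kg: 20 mg/kg
- 70 kg: 14.3 mg/kg
- 100 kg: 10 mg/kg

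This spans the reference range, and 21 of 28 days matches its longer schedule.

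**When 42 g is passed.**
- With preoperative doses: 3 + 21 = 24 g at D21. Cycle 2 starts on D29. Eighteen more doses bring the total to 42 g on D46, so it is exceeded on D47 (43 g).
- Without preoperative doses: 2 × 21 = 42 g on D49. The next dose is on D57.
- Other readings of the printed 1 g, with preoperative doses: D103 at 0.5 g per day and D19 at 2 g per day. All fall within the 168 days of chemotherapy.

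**Total at 24 weeks.** 168 / 28 = 6 cycles; 6 × 21 = 126 g, or 129 g with the preoperative doses. Against the marker, 126/42 = 3.0 and 129/42 = 3.1.

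**The plasma minimum.** 34/0.01 = 3,400 and 45/0.01 = 4,500. The criterion is that many times below the concentrations the article associates with neuropathy.

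**In the plan's favour.** 42 g over exactly 28 days is 1.5 g/day. Table 1 averages 21/28 = 0.75 g/day, which is 50% of that rate. The printed pattern is therefore less intense than the rate implied by the marker, though half of that rate is not a very low dose.

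**The case against.** The strongest reply is that the 1 g is not clearly binding. The Interventions text leaves regimens to centres, Table 1 is titled as a chemotherapy table, and the dose is called hypothetical. This stands, and it is why day 47 and the gram totals are conditional. It does not rescue the rationale: no lower dose is printed anywhere, and centre discretion with only a minimum leaves exposure open upwards.

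Second, the match with the metabolic-disease regimen partly helps the plan, because that regimen is cited as a lifelong recommendation. This also stands. It is an argument that long use at a therapeutic dose has precedent, which differs from the argument that the dose is very low.

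Third, the rationale does not rest on low dose alone, and harm is monitored. The Introduction also relies on resolution after stopping, long-term follow-up and discontinuation for drug reactions. Table 2 ticks safety observation and adverse-event recording from surgery to 48–60 months. The Safety section records adverse events, whether or not related to treatment, until one month after treatment ends. Data monitoring includes a check of dosage, and Auditing provides reviews every 2 to 3 months. These safeguards detect and manage harm; they do not make the exposure statement true.

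A reader might go further and infer that 17.9% of the experimental group would develop neuropathy. The documents do not support that: the figure describes continued use beyond four weeks, and the schedule has a rest week in every cycle. Nor can one infer that 34–45 μg/ml would be reached, because no plasma level at 1 g is given. A reader might also carry the Table 1 pattern through all five years. The table covers 24 weeks, and the later dose may be set out in the full protocol.

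**Conclusion.** The inconsistency is real and should be fixed. As written, the claim of very low dosage does not fit the only printed dose, and a plasma minimum cannot carry a claim of maximized safety. These are faults in the printed text, not detail left to another document.

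The size is conditional. With 1 g as a daily total, preoperative doses counted, D1 as postoperative day 1 and the same dose at all centres, 42 g is passed on about day 47 and 126–129 g is given by week 24. Changing the dose reading or dropping the preoperative doses moves the crossing to between day 19 and day 103. The per-kilogram match rests on assumed weights of 50–100 kg.

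What is established is a wrong description of exposure and a missing upper bound beside the stated lower one. An excess risk of neuropathy is not established. The efficacy endpoint, allocation and analysis are untouched, and existing monitoring limits the consequences, so this falls short of a must-fix.

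**What to change.** 1. In the Introduction, remove the statements that the dose is very low and that the plasma level maximizes safety, or lower the Table 1 dose until they are true. State the expected cumulative grams together with the reading assumed, for example 126–129 g over 24 weeks at 1 g per dosing day. Which statement is right is for the clinical team.
2. Set a maximum daily or cumulative dose beside the 0.01 μg/ml minimum, chosen by the clinical team and binding on any regimen set by a centre.
3. Check for peripheral neuropathy at the physical examinations already in Table 2. Include those in the 1–12-month period: on the printed schedule only 23–26 g has been given by day 30 (21 + 2, plus 3 if preoperative doses count), so the 30-day visit precedes the marker. Tabulate the results by arm at the existing three-monthly monitoring committee review.

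The cost is protocol wording, one dose limit and one case report form item, with no new visit or drug assay. The safety statement becomes less favourable, and a limit may lower exposure in some patients.
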